## Abstract

**Introduction:** Mild cognitive impairment (MCI) not only negatively impacts upon a person's life, but it is also seen as an intermediate stage on the progression to Alzheimer's Disease (AD), and therefore warrants early intervention. However, there is currently no effective pharmacological treatment approved for MCI. There is a paucity of evidence that non-pharmacological interventions such as cognitive training could result in improvements in the daily activities functioning of persons with MCI. Growing evidence has shown that mindfulness meditation increases gray matter volume and concentration in brain regions such as the hippocampus and prefrontal cortex, strengthens brain functional connectivity, and enhances psychological well-being which could be beneficial to counteract the memory and cognitive decline of MCI.

**Aims:** We aim to quantitatively investigate whether mindfulness practice can improve the cognitive function, psychological health, mindfulness and functional abilities in activities of daily living of the MCI participants over time; the relationship between the amount of mindfulness practice and degree of improvement in these health outcomes; and the differential effects and interactions of both formal and informal mindfulness practices. We will also qualitatively address the issues about the MCI participants' and familiar support persons' engagement with the program, the nature of group interactions, their program experience, their perceived effects and expectations of mindfulness practice, and the challenges encountered in practicing mindfulness.

**Methods:** Our study is one of the first mixed-methods longitudinal studies with a 1-year follow-up using a pre- and post-intervention design. It involves the MCI participants and their familiar support person in a customized 8-week group-based mindfulness training program. The outcome measures will use the Montreal Cognitive Assessment, Depression Anxiety Stress Scales, Freiburg Mindfulness Inventory and Bayer Activities of Daily Living Scale. The qualitative methods will include participant observation during the program and semi-structured interviews at post-intervention and 1-year follow-up.

**Significance:** This customized MCI group mindfulness training program presents as a promising and feasible non-pharmacological therapeutic intervention option for MCI and a possible preventive strategy for Alzheimer's disease. This study has been registered in the Australian New Zealand Clinical Trials Registry (ANZCTR) (URL: https://www.anzctr.org.au/Trial/Registration/TrialReview.aspx?id=366695) and allocated the ACTRN: ACTRN12614000820606.

## Introduction

According to the World Health Organization, 47.5 million people worldwide have dementia with an annual incidence of 7.7 million new cases every year. This number is projected to increase to 75.6 million people by 2030 and to 135.5 million people by 2050 (WHO, 2016). Notwithstanding the impact of dementia on the families and caregivers of persons with dementia, the economic burden of dementia was estimated to be US$604 billion in 2010, equivalent to 1% of the worldwide gross domestic product (WHO, 2016). Although dementia is not a natural phase of normal aging, the majority of people with dementia are older people (AIHW, 2015). It has been estimated to be the developed world's third largest burden of disease after depression and ischemic heart disease by the year 2030 (Mathers and Loncar, 2006).

Alzheimer's disease (AD) is the most common form of dementia and comprises 60–70% of cases (WHO, 2016). Mild cognitive impairment (MCI) refers to the transitional state of cognitive changes between normal aging and AD (Petersen et al., 2001). The clinical and cognitive criteria for MCI evaluate negative changes in the individual's cognition compared to his/her previous level. These include objective evidence of impairment in one or more cognitive domains (Albert et al., 2011). One of the most commonly implicated cognitive domains is episodic memory–that is, “conscious recall of events and verbal/visual materials, measured by the ability to recall lists of words or recognize faces both immediately and after a delay” (Henry et al., 2011). Preservation of independence in functional abilities and non-diagnosis of dementia are also important for a diagnosis for MCI (Albert et al., 2011).

Each year, approximately 10–15% of MCI patients converted to AD, compared to the 1–2% annual conversion rate of healthy controls (Petersen et al., 1997, 2001). The MCI sub-clinical population is therefore possibly in “a transitional zone between normal cognition function and clinically probable AD” (Winblad et al., 2004), and should be identified and targeted for early therapeutic intervention.

The risk factors for dementia are essentially the same as those for heart disease (Chen et al., 2014). Preventive approaches are important particularly in light of the fact that while several drugs are used for treating AD, there is currently no effective pharmacological treatment approved for MCI. Studies on pharmacological treatments using cholinesterase inhibitors that are approved by the United States Food and Drug Administration (FDA) and the Australian Therapeutic Goods Administration (TGA), such as donepezil (Aricept®), rivastigmine (Exelon®) and galantamine (Razadyne®, Galantyl®, Reminyl®), on MCI patients to provide short-term benefits for mild to moderately severe AD, have produced mixed evidence with inconclusive results on cognitive improvement or progression from MCI to AD (Vega and Newhouse, 2014).

One other factor contributing to the risk of MCI and AD is poor sleep (Tsapanou et al., 2015). Not only has this been associated with a higher risk of AD but also poorer clearance of beta-amyloid from the brain at night (Mander et al., 2015; Sprecher et al., 2015). Mindfulness training has been found to improve sleep in older adults, suggesting another possible link between mindfulness, MCI and AD (Winbush et al., 2007; Black et al., 2015).

Cognitive training is one of the interventions used in the management of MCI (Henry et al., 2011). However, one Cochrane review concluded that due to the inadequate quality of evidence, the limited effects of performance gains derived from cognitive interventions could not be attributed to specific training effects as these improvements did not exceed those in active control conditions (Martin et al., 2011). Another Cochrane review simply found no significant gains from cognitive training (Bahar-Fuchs et al., 2013). More importantly, the few individual studies that found preliminary evidence of potential benefits derived from cognitive training have not established whether the effects were generalized to the daily functioning of persons with MCI. In light of this, there is a need for therapeutic interventions that specifically target risk factors that could be transferrable to activities of daily living (ADL) for persons with MCI.

Mindfulness can be described as a way of training attention and fostering awareness. This can be done through formal attentional training (mindfulness meditation) or informal practice and applications by being more attentive and engaged in daily life. When unmindful, distracted and inattentive, the brain switches into default mode which has been associated with poor mental health (Brewer et al., 2011) as well as higher amyloid-beta deposition (Simic et al., 2014). Mindfulness training has been found to switch off default mode (Brewer et al., 2011).

Studies have also shown a positive association between amount of meditation practice and meta-cognitive awareness (Garland et al., 2009), attentional performance and cognitive flexibility (Moore and Malinowski, 2009). Early intervention with mindfulness training is therefore a feasible and efficacious non-pharmacological therapeutic intervention option that may improve the cognitive function of persons with MCI and prevent progression to AD. Indeed, there is already growing evidence to suggest that meditation may be a potentially useful and affordable treatment approach for enhancing cognition and memory in patients with neurodegenerative diseases (Newberg et al., 2014). The positive effects of meditation on cognition and dementia risk reduction may be achieved holistically through multiple pathways such as producing neuroprotective effects from less stress-induced cortisol secretion with higher brain-derived neurotrophic factor (BDNF) levels; enhancing lipid profiles and reducing oxidative stress, thereby reducing risk for cerebrovascular/age-related neurodegenerative diseases; and reinforcing neuronal circuits and boosting cognitive reserve (Xiong and Doraiswamy, 2009). Moreover, “studies have demonstrated the effects of mindfulness on enlarging gray matter volume (Pagnoni and Cekic, 2007; Luders et al., 2009), increasing gray matter concentration (Hölzel et al., 2008; Vestergaard-Poulsen et al., 2009; Hölzel et al., 2011; Singleton et al., 2014), strengthening brain functional connectivity (Brewer et al., 2011; Jang et al., 2011; Hasenkamp and Barsalou, 2012; Taylor et al., 2013; Wells et al., 2013b), and enhancing psychological well-being (Singleton et al., 2014), thus suggesting the potential benefits of mindfulness on MCI” (Wong et al., 2015). Mindfulness can thus prevent the “tissue volume loss in the hippocampus and posterior cingulate/precuneus (Buckner et al., 2005; Beason-Held, 2011; Fotuhi et al., 2012; Wang et al., 2013), gradual loss of gray matter (Thompson et al., 2003), reduced functional connectivity in the default mode network (Sorg et al., 2007; Gili et al., 2011; Hafkemeijer et al., 2012; Wang et al., 2013), and high chronic psychological distress (Wilson et al., 2007) that are all implicated in the memory and cognitive decline observed in MCI and AD” (Wong et al., 2015).

Two small pilot clinical studies have been conducted on persons with MCI and dementia using the Mindfulness-Based Stress Reduction (MBSR) course. In the first study, a preliminary assessment of the feasibility of eight 2-h weekly MBSR sessions and one mindfulness retreat day that was conducted using a pilot randomized trial with a small sample of 14 MCI adults, found a non-statistically significant trend toward improvement of cognition and well-being (Wells et al., 2013a). The second pilot study involving 12 persons with dementia and 8 carers again found non-statistically significant improvements in mental well-being after attending eight 2.5-h weekly MBSR course but a non-significant decrease in well-being between post-intervention and 3-month follow-up. Even so, qualitative analyses from course observations and interviews showed that some participants with dementia were able to learn mindfulness and experienced subjective improvements in several quality of life dimensions (Leader et al., 2013).

A key methodological limitation in these studies may be that the generic content of the MBSR course was not customized to the specific needs of the participants with cognitive impairment. There is a lack of longer-term monitoring of the longitudinal effects of mindfulness practice on persons with MCI. Another limitation is the failure to achieve statistical significance because of the small sample sizes in these studies. Finally, the main focus of the MBSR course is on formal mindfulness practice (meditation) and may have insufficiently emphasized the informal mindfulness practice in daily living activities, for example (e.g.,) by incorporating informal mindfulness practice into everyday activities and daily experiences. Such informal mindfulness practice can be tied in with existing ADL (e.g., by encouraging people to eat, travel and communicate mindfully) to promote sustained mindfulness outside of meditation sessions. It would also enhance engagement with ADL, significantly increasing cognitive stimulation throughout the day, which could be assumed to be beneficial for persons with MCI. There is preliminary evidence for this, such as Landau et al.'s study which reported increased cognitive activity such as reading, writing and playing games particularly in early- and middle-life, may directly reduce the beta-amyloid before the onset of AD, as shown that older individuals with high cognitive activity had beta-amyloid comparable to the young controls, while those with low cognitive activity had similar beta-amyloid as the AD patients (Landau et al., 2012).

Overall, the above studies suggest that a longitudinal study into a mindfulness training program that incorporates both the formal (mindfulness meditation) and informal (application in daily living activities) practices of mindfulness, and that is customized to the needs, health outcomes and level of understanding of persons with MCI, is warranted. The proposed study will meet this need.

### Study design

This study adopts a non-randomized pre-/post-intervention design. Persons with a clinical diagnosis of MCI from treating health professionals will receive an 8-week group-based mindfulness training program which is customized to their needs, health outcomes and level of understanding. A follow-up assessment will be conducted one year after the program completion to measure the longitudinal effects of mindfulness practice on persons with MCI over time.

### Research questions

Our hypotheses are:

That mindfulness practice will improve the cognitive function, psychological health, mindfulness and ADL functioning of persons with MCI.The degree of these improvements in cognitive function, psychological health, mindfulness and ADL functioning will correlate positively with the amount of mindfulness practice.

To test these hypotheses, the following quantitative research questions were formulated:

Does mindfulness practice improve the cognitive function, psychological health, mindfulness and ADL functioning of persons with MCI?Does the degree of improvement in cognitive function, psychological health, mindfulness and ADL functioning vary with the amount of mindfulness practice?How much of any observed improvement is due to formal mindfulness practice and how much is due to informal applications of mindfulness to ADL?

Further, this study aims to address the following qualitative research questions:

How do the MCI participants and familiar support persons (FSPs) engage with the mindfulness training program?What is the nature of group interactions between the Mindfulness Trainer and the MCI participants/FSPs and amongst the MCI participants/FSPs during the program?What is the mindfulness training program experience for the MCI participants and FSPs (e.g. was it enjoyable, satisfactory, stimulating and useful)?What perceived effects do the mindfulness training program and mindfulness practice generally have on the health and life of MCI participants and FSPs?What are the challenges faced by MCI participants in implementing and maintaining mindfulness practice?Do the expectations of the MCI participant and his/her FSPs about mindfulness practice match with each other?

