#### Quantitative data

The primary outcome is the change in cognitive function assessed by the Montreal Cognitive Assessment (MoCA) that measures the MCI participants' eight cognitive domains of visuospatial/executive, naming, memory, attention, language, abstraction, delayed recall, and orientation over time. The MoCA has excellent sensitivity of 90%, high test-retest reliability, predictive values, content validity and specificity, and good internal consistency (Cronbach's alpha of 0.83; Nasreddine et al., 2005). The MoCA will be administered by researcher (WW) during all three data collection sessions.

The secondary outcomes measured will be changes in psychological health, mindfulness and ADL functioning. The MCI participants will complete the following self-rated questionnaires during all three data collection sessions:

21-item Depression Anxiety Stress Scales (DASS-21) that measures psychological health on the axes of depression, anxiety and stress on a continuum of severity over the past week (high internal consistency with respective Cronbach's alphas of 0.94, 0.87, and 0.91; Antony et al., 1998); and14-item Freiburg Mindfulness Inventory (FMI) that measures the experience of mindfulness within the past 7 days (high internal consistency with Cronbach's alpha of 0.86, construct validity and sensitivity to change; Walach et al., 2006).

In addition, another secondary outcome measure of ADL functioning will be assessed using the 25-item Bayer Activities of Daily Living (B-ADL) Scale (Cronbach's alpha above 0.98) which will be completed by the FSP who will rate the MCI participant's functional deficits in the performance of everyday activities (Hindmarch et al., 1998; Erzigkeit et al., 2001).

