**Figure 2 F2:**
[figure not shown]
**Framework of the presentation of qualitative and quantitative data**. ADl, Activities of Daily Living; ANOVA, Analysis of variance; FSP, Familiar Support Person; MCI, Mild Cognitive Impairment.

The MCI participants and FSPs have the option to receive an email containing a summary of the non-identifiable group results when this study is completed. The findings from this study will be disseminated through peer-reviewed academic journal publications and presented at national and international seminars and conferences. In any publication and presentation, the information will be presented in non-identifiable form to protect the privacy of the MCI participants and their FSP.

It is expected that the mindfulness training intervention will proactively engage the MCI participants early and yield the practical application of improving their cognitive function such as attention and memory if they maintain mindfulness practice over time. There may be a potential benefit of delaying the progression of MCI to AD but this will not be assessed in this study. In addition, other expected improvements in psychological health, mindfulness, and in functional abilities of ADL may also indicate better health outcomes of mindfulness for MCI. This study will contribute toward the clinical research of MCI and advance evidence-based knowledge about the effects of long-term mindfulness practice as a promising and feasible non-pharmacological therapeutic approach for persons with MCI. This could potentially translate to downstream significance of better quality of life and higher work productivity of persons with MCI and their FSP, and a reduced chronic disease burden on families of persons with MCI and the healthcare system. If effective, “partnerships could be eventually forged with the Alzheimer's Australia and memory clinics/services such as the CDAMS to deliver the customized group mindfulness training program to the target population of persons with MCI and their FSP” (Wong et al., 2015).

The study findings could open a potential future research direction to explore the use of biomarkers such as beta-amyloid and tau proteins to monitor the longitudinal effects of mindfulness practice on the cognitive and functional progression of persons with MCI and the conversion rate from MCI to AD.

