## Potential pitfalls and counteracting measures

This study was originally designed as a randomized controlled trial using pre- and post-intervention design that will assign persons who have been clinically diagnosed with MCI to either the 8-week mindfulness training intervention group or the “standard care” control group. In the original randomized controlled trial design, the estimated total sample size is 166–83 MCI participants in the intervention group and 83 in the control group, in order to achieve 80% power for a two-tailed test at the alpha level of 0.05 with a medium effect size of 0.50. The minimum sample size required to detect a clinically significant difference is 68 participants–34 in each of the two groups. This design was approved by the Melbourne Health Human Research Ethics Committee. However, due to the challenges in the study recruitment of MCI participants, changes had to be made to the randomized controlled trial study design to that of a pilot study that would explore the feasibility of the mindfulness training intervention for future research. Consequently, the revised target sample size is about 20 MCI participants. An estimation of 80 interviews conducted with 20 MCI participants and 20 FSPs at T1 and T2, and coupled with participant observation of the mindfulness program produce rich qualitative data and provide important participant perspectives such as learning and maintaining a new behavior, that could yield significant contributions to the field (Morse, 2000; Creswell, 2007), especially in this sub-clinical population that is under explored. The findings would be relevant to better understand this population, help future study recruitment, and shed insights to further research studies with this population. This revised study design was also approved by the Melbourne Health Human Research Ethics Committee.

As the age profile of the MCI participants is senior (at least 60 years old), program attendance and participation might be affected by various circumstances such as clinically significant scores of cognitive impairment measured by MoCA and of psychological health measured by DASS-21, conversion to dementia such as Alzheimer's disease, and pre-existing medical conditions. The research team will review the participants' continued study participation and notify their GP or treating health professional for follow-up after discussion with them.

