The MCI participants are required to attend at least six of the eight sessions to have satisfactorily completed the mindfulness training program. The MCI participants and FSPs are provided with the program manual and the mindfulness practice audio CD, and researcher (WW) contacts the MCI participants weekly during the program duration to discuss any questions, concerns and issues that they might have. WW will also inform the outline of the weekly module to those who have missed the session.

To encourage the MCI participants to do their mindfulness practices and obtain their monthly practice record forms, researcher (WW) will contact them on a monthly basis after their completion of the mindfulness training program. However, due to the extent of cognitive impairment of certain MCI participants, particularly for those who are not living with their FSP, WW might have to contact them more frequently to better support them. Such study rigor might impose some inconvenience on these MCI participants. Thus, WW will check with them on their comfortable frequency of post-intervention communications such as fortnightly phone calls.

The MCI participants and FSPs are free to withdraw consent from the study at any stage by informing the research team which will still include the previous data and information that are already collected from them in the data analyses to form part of the study findings.

While the study findings from this reasonably homogeneous sample may be potentially positive, however, due to the small sample size, it is not likely to reach statistical significance. As such, the study will also share the similar study limitation of small sample sizes in previous studies and its results may not be generalizable to the broader community.

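### The control arm was dropped but hypothesis 1, questions 1 and 3 and the time-point comparison still attribute pre/post change to mindfulness, and the limitations do not name the missing comparator

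*Protocol article*

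**What the plan says.** Study design: "This study adopts a non-randomized pre-/post-intervention design". All participants receive the eight-week programme, with assessments before it (T1), after it (T2) and one year later (T3).

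Research questions: hypothesis 1 states that practice will improve cognition, psychological health, mindfulness and daily functioning. Question 1 asks "Does mindfulness practice improve the cognitive function, psychological health, mindfulness and ADL functioning of persons with MCI", and question 3 asks "How much of any observed improvement is due to formal mindfulness practice and how much is due to informal applications of mindfulness to ADL". Hypothesis 2 and question 2 speak only of correlation or variation with the amount of practice.

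Outcome measures: the primary outcome is change in MoCA. One researcher administers it at all three sessions and also observes all eight programme sessions.

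Stepwise procedures: the comparison across time points is described as one of the effects of mindfulness. The section recognises that MCI may stay stable, improve or worsen, but only when it discusses consent and continued participation.

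Potential pitfalls and counteracting measures: the trial was first designed as randomised against standard care. Recruitment difficulties turned it into a "pilot study that would explore the feasibility of the mindfulness training intervention for future research", with a target of about 20 participants. The limitations paragraph says of a positive finding that "due to the small sample size, it is not likely to reach statistical significance", and adds that results may not generalise.

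**The concern.** The design changed and the claims did not. With a concurrent control, a shift common to both arms cancels. In a single arm it remains in the estimate, and nothing in the planned within-person analysis removes it.

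Question 3 goes furthest. It divides all of the observed improvement between two kinds of practice and leaves no share for anything else.

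The limitations then point the reader to the wrong remedy. If small numbers are the only weakness named, a significant result would appear to overcome it, and a larger single-arm study would appear to be the next step. Neither follows. The Introduction shows that the issue is understood: it reports that gains from cognitive training "could not be attributed to specific training effects as these improvements did not exceed those in active control conditions". That remark concerns another intervention, but the reasoning about comparators applies here as well.

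**Working it through.** **1. Plan's own figure.** The current design of about 20 participants has no power statement, so there is no figure to reproduce. The 166 in the pitfalls section belongs to the superseded randomised design and does not bear on this point.

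**2. What could produce a change from T1 without any effect of mindfulness.**

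| Source | Where it arises | Treated as a limit on interpretation? |
|---|---|---|
| Retest learning | MoCA given three times (Quantitative data) | No |
| Fluctuation of MCI | Stepwise procedures | No, only for consent and participation |
| Non-specific contact | Weekly group sessions; weekly, then monthly reminders and calls | No |
| Assessor expectation | MoCA assessor attends every session and makes the support contacts | No |
| Natural decline by T3 | Introduction cites 10–15% yearly conversion to AD | No |
| Health and lifestyle | Measured at all three sessions | Yes, named as potential confounders |

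The first four could raise scores (fluctuation could go either way). Decline would lower them and could hide a real benefit at T3.

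**3. Illustration of size.** Inputs: n = 20 (article) and two-sided alpha 0.05 (article). The retest gain of 0.5 to 1.0 MoCA points and the SD of change of 2 points are assumptions; the article gives neither. The true effect of mindfulness is set to zero.

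- Standardised shift: dz = gain / SD of change = 0.5/2 = 0.25 and 1.0/2 = 0.50.
- Noncentrality: dz × √20 = 1.118 and 2.236. Critical t on 19 df: 2.093.
- Probability of a significant paired test (noncentral t): 18.6% and 56.5%. Nearly all of this lies in the direction of improvement (18.5% and 56.4%), where the nominal rate is 2.5%.

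**4. Does a larger sample help?** With the same dz, noncentrality grows as √n:

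| n | dz = 0.25 | dz = 0.50 |
|---|---|---|
| 20 | 18% | 56% |
| 40 | 34% | 87% |
| 80 | 60% | 99% |

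(Probability of a significant improvement with no treatment effect.) A larger sample makes the false attribution more likely. With a concurrent control sharing the same shift, the rate would stay at 2.5%.

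**5. Sensitivity.** Take instead a shift g in SDs of the score and a retest correlation r, so that dz = g / √(2(1 − r)). At n = 20, g = 0.1 gives 8 to 16% for r from 0.7 to 0.9, g = 0.2 gives 19 to 48%, and g = 0.3 gives 38 to 81%. The direction is the same throughout; the size depends on the inputs.

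**6. Can the regression on practice stand in for a control?** No. Participants choose how much they practise, and those whose cognition is holding up may practise more. Entering age, gender and education does not remove that. Question 2 is rightly worded as association; question 3 is not.

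**The case against.** The article calls the study exploratory and a pilot, says that possible effects need further research, expects trends rather than significance, and discloses why randomisation was abandoned. It measures health and lifestyle factors and examines them against the outcomes. This counts in its favour and bears on severity. But the exploratory label is used to justify leaving the type I error unadjusted, not to soften the causal questions, and lifestyle covariates do not address retesting or contact.

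The illustration uses a plain paired test, whereas the plan specifies repeated measures ANOVA on the relative effects of formal and informal practice, and its inputs are assumed. Both points stand, so it shows scale only. The assessor point applies to the MoCA alone: DASS-21 and FMI are self-rated, and the B-ADL is completed by the support person.

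A reader might infer more than the article supports:

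- *That any rise will be reported as benefit.* The text does not say so. What holds is that a rise cannot be told apart from benefit.
- *That regression to the mean is built in.* Entry is by prior clinical diagnosis, with no MoCA cut-off at T1, so it is not shown.
- *That feasibility goes unexamined.* Recorded attendance, the six-of-eight completion rule, the adherence questionnaire, practice records and interviews all bear on it. Making feasibility the primary objective would be a design preference.
- *That the abstract contradicts the later text on prevention.* Its wording is hedged, and Anticipated results says openly that there may be a benefit of "delaying the progression of MCI to AD but this will not be assessed in this study".

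**Conclusion.** The point holds in this form: hypothesis 1, questions 1 and 3 and the phrase in Stepwise procedures claim what a single-arm design cannot show at any sample size, and the limitations omit the reason. That conclusion follows from the design and needs no assumed number.

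The size does rest on assumptions. With a retest gain of 0.5 to 1.0 points and an SD of change of 2, about 19 to 56% of 20-person studies would show a significant change with no treatment effect. From T2 to T3 decline may push the other way, so the bias is not always towards benefit.

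This should be fixed. It governs what the study may conclude, but in a declared exploratory pilot the remedy is wording and reporting, not a new design.

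**What to change.** 1. Reword hypothesis 1, questions 1 and 3, and the comparison in Stepwise procedures as change over time among programme participants and its association with self-chosen formal and informal practice. Hypothesis 2 and question 2 can stay.
2. State that no causal effect of mindfulness will be concluded from within-group change.
3. Add to the limitations: no comparator, retest learning, fluctuation and decline of MCI, contact time, and an unblinded MoCA assessor.
4. Serve the stated feasibility purpose by reporting attendance at six or more of the eight sessions, return of practice record forms and retention at T3, each with a confidence interval. For example, 16 of 20 would have an exact 95% interval of 56 to 94%.
5. Present MoCA change with its interval as an estimate for a future controlled trial.
6. Optionally, use alternate MoCA versions across the sessions if they are available.

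The cost is text edits and a few extra summaries from data already being collected. No participants or staff are added. The claims become more modest.
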